### Analyses

Analysis of primary endpoints will compare rate of ASH admissions between treatment groups followed by other main endpoints. Simple unadjusted rates, relative risks and 95% confidence intervals will be obtained initially, with subsequent multiple regression analysis adjusting for paired randomisation and other variables. Negative binomial regression will be used. Baseline rates will likely be included as a covariate in regression models as pre-intervention hospitalisation rates will be highly predictive of post-intervention rates.

Sub-group analyses to check for effects that differ from the overall treatment effect will be performed for the following:

• facilities classed as charitable, religious or welfare facilities vs. for “for profit” facilities

• for facilities that have only rest-home beds vs. those with both rest-home and hospital beds

• for long-stay vs. short-term (e.g. respite or palliative care) residents

• for facilities providing after-hours primary care cover through either their usual GP or a contracted after-hours primary care provider, vs. those without such cover (effectively using ambulance and emergency department for after-hours primary care)

All main analyses will be formally analysed on an "intention to treat" basis. Tests of significance will be two-tailed. Analysis of secondary outcomes will use standard statistical procedures applicable to categorical, continuous, or failure-time data as appropriate.

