## Methods/design

This is a randomised controlled trial of a complex intervention of a package of supports and services provided by District Health Boards (DHBs) interdisciplinary team outreach to RAC facilities.

The study is taking place in the greater Auckland area of New Zealand. Auckland is the largest metropolitan area of New Zealand with a population of 1.4 million people. Within this region there are 175 aged care facilities, from which the participating facilities were selected on the basis of higher than ‘expected’ hospital admission rates. A total sample size of 1400 resident-years was originally anticipated to provide 80% power (5% significance) to detect a 25% reduction in rate of ASH hospitalisations in the intervention group compared to the control group when an event rate of 60 events per 100 years was expected. However, observed event rate in another cohort after commencement of the trial showed a lower event rate, so power estimates were recalculated. With 18 facilities for each group each with 14 months of follow-up, an average of 38 beds per facility and bed occupancy of 90%, we expect a total of 1500 resident years of follow-up. Revised power is estimated at 53%, considering:

• Inflated sample size as the design effect of 2.0 will allow for moderate intracluster correlation for hospitalisation rates of 0.025
[23,24]

• Rate of 35 ASH admissions per 100 resident years in control facilities vs. 26 ASH admissions in intervention facilities, assuming a Poisson distribution where the mean equals the variance. The control event rate was estimated from re-analysis of the RACIP study (Boyd et al., 2008) and the OPAL study cohort (results not yet published).

However, we anticipate an improvement in power because;

• the facilities were chosen (from statistical modelling) for their higher event rates (e.g. an event rate of 0.40 would provide power of 0.67)

• short-stay residents (under-represented in OPAL-based rates) have a higher event rate

• adjustment for covariates in our analysis will reduce confidence intervals around effect size

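### The Analyses section names its methods without a unit of analysis or any account of facility clustering, although facilities are randomised and the power calculation assumes a design effect of 2.0

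*Protocol article*

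**What the plan says.** **Design.** The Randomisation section of the protocol article allocates 36 facilities, not residents.

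**Power.** The sample-size text under Methods/design takes clustering as real: "Inflated sample size as the design effect of 2.0 will allow for moderate intracluster correlation for hospitalisation rates of 0.025". It works with yearly admission rates of 0.35 and 0.26 per resident in the two arms, takes the counts as Poisson, and arrives at a revised power of 53%.

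**Analysis.** The Analyses section is specific about several things. It gives an order: "Simple unadjusted rates, relative risks and 95% confidence intervals will be obtained initially". It then plans a multiple regression adjusted for the pairing and other covariates, and names the model: "Negative binomial regression will be used". Baseline rates are a probable covariate, and "Tests of significance will be two-tailed". It does not give a facility random effect, a cluster-robust variance, or a statement of whether the model is fitted to residents or to facilities.

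**Hints about the unit.** These point both ways. Outcome measures expresses the first outcome as a share of residents admitted and plans sub-groups by age and gender; Analyses adds long-stay against short-term residents. Against that, hospital days are expressed per occupied bed, control follow-up is tied to a paired facility, and three of the four sub-groups listed under Analyses are facility characteristics.

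**The concern.** In a cluster-randomised trial the treatment contrast carries the variance between facilities. An analysis that leaves this out understates the standard error, and chance differences between 18 and 18 facilities are declared significant too often.

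The terms that the section does name do not reliably supply the missing piece:

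- A crude relative risk with its usual interval treats admissions, or residents, as independent.
- In a negative binomial model fitted to residents, the dispersion parameter describes how residents differ from one another. It does not describe the correlation of residents in the same facility.
- Adjusting for pairs can remove part of the between-facility variance. Treatment differs between the two facilities of a pair, however, so the difference between them stays in the treatment contrast. The Randomisation section also describes stratification by health board and care mix, not pairing, so the content of this term is uncertain.

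At stake is whether the main test keeps its 5% level. As worded, the section admits one analysis that roughly does and another that runs at about three times that level.

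**Working it through.** **Inputs, all from the protocol article.** 36 facilities, 18 per arm; 1,500 resident-years; 38 beds at 90% occupancy; 1,700 residents (Abstract); ICC 0.025; design effect (DE) 2.0; rates 0.35 and 0.26 per resident-year; two-sided 5%.

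**1. Does the stated power include clustering?** Effective resident-years per arm = 1500 / 2 / 2.0 = 375. With the control-arm Poisson variance in both arms and an exact 25% reduction (0.35 to 0.2625):

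- SE = sqrt(2 × 0.35 / 375) = 0.0432
- 0.0875 / 0.0432 = 2.025; 2.025 − 1.960 = 0.065; power = 52.6%

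This reproduces the stated 53%. With 0.26 in place of 0.2625 it is 54.9%. With arm-specific variances at 0.35 and 0.26 it is 60.7%.

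Without the design effect, the first formula has SE = sqrt(2 × 0.35 / 750) = 0.0306 and 0.0875 / 0.0306 = 2.864, so power is about 82%. The arm-specific version gives 88%. The stated 53% therefore does include clustering.

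**2. Range of the design effect.** DE = 1 + (m − 1) × 0.025:

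- m = 38 × 0.90 = 34.2 residents: DE 1.83
- m = 1500 / 36 = 41.7 resident-years: DE 2.02
- m = 1700 / 36 = 47.2 residents: DE 2.16

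**3. Error rate if clustering is left out.** True two-sided error = 2 × (1 − Φ(1.96 / sqrt(DE))):

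| DE | SE too small by a factor of | Two-sided error |
|---|---|---|
| 1.83 | 1.35 | 14.7% |
| 2.0 | 1.41 | 16.6% |
| 2.16 | 1.47 | 18.2% |

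At DE 2.0 a nominal 95% interval covers about 83%.

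**4. Allowance for covariates (assumption).** If pairing and baseline rates removed half of the between-facility variance, DE would fall from 2.0 to 1.5 and the error to about 11%.

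**5. Check by simulation.** Null trials with 36 facilities and gamma variation between them, 1,200 runs per setting; percentage rejected at a nominal 5%:

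| Setting | Facility totals, NB (z) | Facility totals, NB (t, 34 df) | Residents, NB, no facility term | Crude Poisson interval |
|---|---|---|---|---|
| DE 1.83 | 6.2 | 5.4 | 15.3 | 15.8 |
| DE 2.0 | 5.8 | 4.9 | 15.7 | 16.2 |
| DE 2.15 | 7.2 | 6.2 | 18.5 | 19.0 |
| DE 2.0 plus resident heterogeneity | 7.0 | 6.1 | 13.3 | 19.6 |

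Fitted to facility totals, the dispersion parameter takes up the between-facility variance and the test stays near 5%. Fitted to residents, it does not.

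**6. Sub-groups.** The design effect depends on how many residents of the sub-group each facility contributes. A sub-group of half the residents has m of about 20.8 and DE = 1 + 19.8 × 0.025 = 1.50, so its treatment comparison would run at about 11% rather than 16.6%.

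**The case against.** The strongest reply is that the section is silent, not wrong. Nowhere does the article say that residents will be treated as independent. An article condenses its plan, and the form of the cluster adjustment is a detail often left to the full document. The named model is also compatible with a sound analysis: on 36 facility totals it holds about 5-7%. The accepted 53% power suggests that the investigators mean to respect clustering, since the same formula gives about 82% without it. Baseline adjustment, which the authors expect to be strongly predictive, would reduce any inflation.

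Much of this stands. A reader might infer that the planned model ignores facilities and that the trial's 5% test will certainly run at 15% or more. The document does not support that: the unit of analysis is open, and the inflation belongs to one reading of the regression, not to negative binomial regression as such. Nor does the document make the crude ratios the primary result; it only obtains them first.

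What remains is more than a missing detail. The section lists its model, adjustment terms, probable baseline covariate, sidedness and order of analysis, and nothing in that list carries the design effect on which the power rests. Baseline adjustment is only probable, and it would not help the crude intervals. The sub-groups by age, gender and length of stay need resident data, or several rows per facility, and either way a cluster term is needed.

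**Conclusion.** The point holds in conditional form. The Analyses section does not fix the unit of analysis or say how facility clustering enters, and this does not match the power section's design effect of 2.0.

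- **Crude intervals as usually computed, and any regression on residents without a facility term:** standard errors too small by about 1.4 at DE 2.0, and a two-sided error of about 15-18% before covariate adjustment. This rests on the plan's ICC of 0.025 and on 34 to 47 residents per facility. Resident-level sub-groups are affected in the same way, to a smaller degree where each facility contributes fewer residents.
- **With covariates:** about 11% if pairing and baseline rates removed half of the between-facility variance, a share that the document does not give.
- **Regression on 36 facility totals:** about 5-7%, with no material problem.

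The validity of the main test depends on which of these is run, so the choice should be written down before the data are analysed.

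**What to change.** Add to the Analyses section a statement that all treatment comparisons, including the unadjusted relative risks with their intervals and the sub-group analyses, account for the facility as the cluster. Name one of these routes:

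- negative binomial regression with a log person-time offset and a random intercept for facility, or with a cluster-robust variance and a small-sample correction; or
- a facility-level analysis of the 36 rates, with a t reference distribution based on the number of facilities.

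The cost is a sentence of text and, for the regression route, one model term or variance option. Where residents would otherwise have been analysed as independent, intervals become up to about 40% wider (sqrt(2) = 1.41 at DE 2.0). The power section already assumed that width, so no precision that the plan counted on is lost.

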## Discussion

This study is designed to provide an intervention to support clinical decisions about at-risk RAC residents and to improve quality of care. The aim is to increase early identification of potential health issues thus improving resident health and reducing avoidable emergency department presentations and hospital admissions. It will inform appropriate, cost-effective use of acute services and will promote access to proven interventions and practice-orientated decision making. It is intended that this study will impact on policy and on planning and financing models of residential aged care, and will increase continuity of care between residential care, primary and secondary care.

This project has potential to lead to the redesign of systems and also to refine policies such as care practices, staffing levels and patterns (night-staffing, after-hours medical care and advanced nursing interventions). It is also hoped that the study will facilitate:

• improved integration of RAC with geriatricians and with emergency/acute services;

• clinical education for RAC staff in facilities to increase their use of research and current guidelines;

• improved RAC palliative care practices;

• alternative residential aged care models to provide targeted care for high risk groups, e.g.: those with end-stage dementia

Other new models may include short RAC stays for rehabilitation and aged care community integration. Reducing hospitalisations will benefit older people residing in RAC because acute hospitalisation may increase the risk of disability and death
[26]. There is evidence that where treatment is offered in situ, residents recover more quickly, reducing confusion and deterioration
[14,27].

The issues that this trial addresses are not unique to Auckland or indeed to New Zealand. Identification and targeting of high admission facilities and refinement of proven interventions directed toward those facilities and modified individually in situ, means that the results of this RCT are likely to be widely applicable internationally.
